## Abstract

**Background:**

The wearing-off phenomenon in patients with Parkinson’s disease (PD) is a complication of prolonged levodopa usage. During this phenomenon, motor symptoms such as rigidity and freezing re-emerge. This is often accompanied by non-motor symptoms, including anxiety, the so-called wearing-off related anxiety (WRA). Current treatment options are limited and typically focus on either the physical or mental aspects of wearing-off. An integrated approach seems warranted in order to optimally address the complex reciprocal interactions between these aspects. Also, because wearing-off is eventually inescapable, treatment needs to focus on coping, acceptance, and self-efficacy. We therefore developed an integrated body awareness intervention, combining principles from physical therapy with acceptance and commitment therapy to teach patients to deal with WRA. This study will investigate whether this new intervention, named BEWARE, is more effective than treatment as usual in increasing self-efficacy.

**Methods/Design:**

This is a single-blinded randomized controlled trial in 36 PD patients who experience WRA. Subjects will be recruited from the outpatient clinic for movement disorders of the VU University Medical Center. After providing written informed consent, patients will be randomly assigned to an experimental (BEWARE) or treatment-as-usual (physical therapy) group. Clinical assessments will be performed prior to the intervention, directly after the 6-week intervention period, and at 3-month naturalistic follow-up by a blinded investigator not involved in the study. The primary outcome measure is self-efficacy, and secondary outcomes focus on mobility, daily functioning, anxiety, and quality of life.

**Discussion:**

Because wearing-off is an inevitable consequence of levodopa therapy and current treatment options are insufficient, a multidisciplinary intervention that addresses both physical and mental aspects of wearing-off in PD may foster additional benefits for treating WRA in PD patients over mono-disciplinary care alone.

**Trial registration:**

ClinicalTrials.gov identifier: NCT02054845. Date of registration: 30 January 2014.

## Background

Parkinson’s disease (PD) is a progressive neurodegenerative disorder of the central nervous system and has a prevalence of 1.6 % among people who are at least 65 years old [1]. The neurobiological hallmark of PD is a loss of dopaminergic cells, causing the typical motor symptoms such as tremor, rigidity, slowness of movement, postural instability, and freezing. Non-motor symptoms, such as autonomic failure, fatigue, depression, and anxiety are also prevalent and this is likely due to an additional involvement of non-dopaminergic systems [2].

To supplement the shortage of dopamine, levodopa treatment is currently the most applied and effective symptomatic treatment [3]. When the dopamine replacement therapy (DRT) takes effect and symptoms become less prominent, the patient is in the ‘on’ state. In contrast, the state in which the patient is in need of a new dose of dopamine and experiences intensified PD symptoms is referred to as the ‘off’ state. A re-emergence of PD symptoms, shifting from an ‘on’ state to an ‘off’ state, is called wearing-off. This typically occurs prior to the next scheduled dose of dopaminergic therapy taking effect [4] and is related to longer disease duration [5].

Motor and non-motor symptoms have reciprocal influences [6]. About 75 % of patients with motor fluctuations, including wearing-off, experience mood or anxiety fluctuations or both in parallel [7]. This wearing-off related anxiety (WRA) is characterized not only by subjective feelings of anxiety but also by physical complaints, such as sweating, abdominal distress, and shortness of breath. Rutten et al. [8], by performing a factor analysis on the Beck Anxiety Inventory (BAI), showed that anxiety symptoms in PD show significant overlap with both autonomic and motor symptoms. This finding demonstrates that physical and mental symptoms are intertwined in PD.

The physical symptoms accompanying WRA are often incongruent with the actual severity and physical impact of motor symptoms of wearing-off, suggesting an increased sensitivity and reactivity to the occurrence of wearing-off symptoms and heightened body awareness in these patients. Body awareness involves a focus on and awareness of internal bodily sensations [9]. An abnormal increase in body awareness can be maladaptive [9] and is, in general, also related to anxiety disorders [10–14].

The anxiety symptoms experienced by patients with PD are often responsive to dopaminergic medication [15]. Therefore, the first therapeutic approach for treating WRA is to optimize the DRT [16]. As the disease progresses, increasing dopaminergic medication (both frequency and dosage) becomes insufficient and complicated because of the increased occurrence of dyskinesias [17]. Also, random fluctuations appear to be more difficult to treat with pharmacotherapeutic approaches because they are unpredictable and not directly related to a lower level of dopamine [17].

Non-pharmaceutical approaches include exercise programs and physical therapy. These have been shown to improve motor problems, daily functioning, and quality of life in patients with PD [18–21]. Though effective for improving mobility-related problems, current physical rehabilitation approaches typically do not offer tools to address the non-motor symptoms of wearing-off.

Cognitive behavior therapy (CBT), mindfulness, and acceptance and commitment therapies (ACTs) have proven to be effective in reducing anxiety symptoms and avoidance behavior in patients with anxiety disorders, also enhancing quality of life [22, 23]. Therefore, classic tools from CBT and ACT might be useful in the treatment of the debilitating effects of WRA. A reduction of anxiety symptoms in patients with PD is observed in most of the CBT studies [24–26]. However, based on clinical experience, efficacy of classic CBT is limited in PD care because the cognitive methods are suboptimal in addressing the interaction between non-motor and motor symptoms during wearing-off. Moreover, the classic approaches aim to reduce the symptoms, whereas the inevitability of motor and non-motor fluctuations in PD demands the ability to maintain physical and mental balance despite the presence of those fluctuations. This is of great importance mainly in the more advanced stages of PD, in which symptom management is more challenging [3]. Therefore, interventions need to focus on independence and self-efficacy more than on reducing symptoms.

To address both the physical and the mental aspects of PD, Wahbeh et al. [27] reviewed mind-body interventions in the treatment of PD and showed that participating in tai chi classes improved the patients’ physical condition. Landsman-Dijkstra et al. [28] tested a highly structured and standardized 3-day body awareness program in 14 participants who had chronic non-specific psychosomatic symptoms. Increases of body awareness, self-efficacy, and quality of life were found after the intervention. However, the researchers did not implement a control group in this study.

Mindfulness-based therapies have proven to be effective in many patient groups, such as patients with chronic pain, anxiety, and depressive disorders, by improving psychological functions and reducing pain and stress [29, 30], although the mean effect size was small (0.42) [30]. In addition, Åkerblom et al. [31] showed that pain-related acceptance is the strongest mediator in CBT treatment in patients with chronic pain. The authors conclude that targeting of acceptance in treatment may lead to further improvements in outcome measures. It has been shown that CBT is effective in PD patients even after a follow-up period on anxiety and coping measures [32]. Because PD is a chronic disease and is accompanied by both physical and mental symptoms (motor and non-motor symptoms), combining mindfulness-based therapy with physical rehabilitation might be of potential benefit for PD patients with WRA.

BEWARE is an integrated body awareness intervention, combined with ACT, in which mindfulness training is incorporated with physical therapy. We will test the effectiveness of this intervention—compared with treatment as usual (TAU)—in terms of self-efficacy in PD patients with WRA. We hypothesize that the BEWARE intervention will be more effective than physical therapy alone (TAU) in improving self-efficacy.

## Methods/Design

### Study design

This will be a single-blind randomized controlled trial. Thirty-six PD patients who experience WRA will be randomly allocated either to the BEWARE training group (*n* = 18, three groups of six patients) or to a control group receiving physical group therapy, which is a usual form of treatment for wearing-off in patients with PD at the VU University Medical Center (*n* = 18, three groups of six patients). Block randomization is done by using concealed opaque envelopes. All participants are asked to maintain the regular medication schedule during the 6-week intervention. Assessments are conducted prior to the intervention and at 6 weeks directly after the intervention. Also, long-term effects will be assessed at 18 weeks of follow-up (from post-enrolment). The assessments will be performed by a blinded investigator who is not involved in the intervention or randomization. Figure 1 demonstrates the study design according to the CONSORT (Consolidated Standards of Reporting Trials) statement [33].

**Fig. 1 Fig1:**
[figure not shown]
Study flow chart. *BEWARE* body awareness training, *PD* Parkinson’s disease, *TAU* treatment as usual

### Patient recruitment

The patients will be recruited from the outpatient clinic of the VU University Medical Center. The neurologists and psychiatrist will be asked to approach PD patients who, in their view, experience WRA. In addition, an announcement will be placed on the website of the Dutch Parkinson patient association (Parkinson Vereniging) and in their magazine. Inclusion and exclusion criteria are listed below.

### Patient inclusion criteria

Given a diagnosis of idiopathic PD according to the UK PD Brain Bank criteria [34].Experiencing wearing-off symptoms or response fluctuations (or both), as measured with the Wearing-Off Questionnaire 19 [35]. A patient is considered to be experiencing wearing-off if he or she indicates at least one symptom that improves after taking a next medication dose.Presence of clinically relevant anxiety, defined as a BAI score of more than 26 [36].

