#### Secondary outcome measures

The Parkinson’s Disease Questionnaire-39 (PDQ-39)

This questionnaire is a measure of quality of life adapted for people with PD [42]. It consists of 39 statements that cover eight domains associated with health, such as mobility and emotionality, that can be influenced by PD. Patients can reply by ticking the relevant answer that indicates whether they experienced problems during the past month (five boxes from ‘never’ to ‘always’). The PDQ-39 is a valid and reliable instrument for patients with PD [42, 43].2.The Wearing-off Questionnaire 19 (WOQ-19)

In this 19-item questionnaire [35], patients with PD indicate which symptoms they experience and whether these symptoms improve after administration of PD medication.3.Beck Anxiety Inventory (BAI)

This self-report questionnaire consists of 21 common symptoms of anxiety [36]. Patients indicate how much they have been bothered by these symptoms during the past week, including today.4.Beck Depression Inventory

This 21-item self-report questionnaire measures whether patients experience depressive symptoms [44]. Patients indicate the statements that are most applicable to their own situation during the past week, including today.5.10-Meter Walk Test (10MWT)

To measure comfortable walking speed, the patients are asked to walk 10 metres, which are characterized by a starting and a finishing point [45]. The researcher measures the time needed to cover this distance.6.Timed One-Leg Stance Test (OLST)

This test measures balance by asking the patients to stand on one leg without help [46]. The number of seconds that the patients maintain their balance is noted; the maximum is 60 seconds.7.The Nottingham Extended Activities of Daily Living (NEADL) index

This 22-item self-report questionnaire covers four aspects of daily living: mobility, activities in the kitchen, domestic tasks, and leisure activities [47]. Patients indicate whether they independently performed activities during the past weeks.8.Freezing of Gait (FOG) questionnaire

This six-item questionnaire is used to identify current problems with walking and symptoms of freezing [48]. For each item, patients indicate which of the five statements is most applicable.9.Visual Analogue Scales (VASs)

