#### Data analysis

To promote data quality, double data entry will be used. Multiple imputation will be applied on missing data. Analysis of variance with repeated measures will be used for normally distributed outcomes at interval and ratio level. Friedman’s non-parametric repeated measures test will be applied for outcomes with non-interval or ratio scale level or for non-normally distributed variables. Factors in the analysis will be group (two levels: control and experimental) and time (three levels: baseline, assessment at week 6 (directly post-treatment), and assessment week 18 (3-month follow-up)).

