### Discussion (expected results)

Wearing-off is an inevitable and disabling consequence of long-term DRT in patients with PD, and WRA is a concept characterized by a complex reciprocal interaction of motor and non-motor symptoms. The general neglect of these complex interactions in the TAU leaves a gap for treatment innovation. BEWARE is a promising therapy for WRA in PD because it specifically focuses on the interaction between physical and mental symptoms. The specific and unique combination of elements of the therapy aims to increase self-efficacy by strengthening one’s own belief to adequately cope with the wearing off and the disproportional concurrent feelings of anxiety rather than reduce or eliminate symptoms.

Because the development of wearing-off is associated with long-term treatment of PD with DRT as well as with an early onset of disease, longer disease duration, and higher doses of levodopa [5, 17, 51], we will inadvertently include patients who are in a more advanced stage of the disease. Therefore, we must pay specific attention to the potential additional difficulties with patient compliance regarding the amount of effort and commitment we demand from the patients during the twice-weekly intervention.

Considering previous research in combination with our own experience based on a small open pilot study in four patients with PD (results not published), we expect to see a significantly bigger improvement in self-efficacy in the BEWARE condition as compared with the TAU condition. In the pilot study, we observed a decrease in BAI total score in the participating patients. In addition, they reported very positive subjective effects of the intervention. In particular, the group aspect and the holistic approach to address WRA were highly appreciated. Patients stated that they were better able to cope with wearing-off after the intervention period. Considering these first experiences, we believe that BEWARE has the potential to be implemented into health-care practices once its value has been established by using proper testing with high methodological standards.

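### The BAI is both entry threshold and outcome: if the qualifying score serves as baseline, regression to the mean can produce a significant time effect, and Friedman's test offers no between-arm comparison to correct it

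*Protocol article*

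**What the plan says.** Patient inclusion criteria, protocol article: "Presence of clinically relevant anxiety, defined as a BAI score of more than 26". The same questionnaire is the third secondary outcome. Under Secondary outcome measures it is a self-report of 21 symptoms: "Patients indicate how much they have been bothered by these symptoms during the past week, including today".

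Data analysis sets the rule for all outcomes. Normally distributed outcomes on an interval or ratio scale go to repeated-measures analysis of variance. For the rest, Friedman's "non-parametric repeated measures test will be applied for outcomes with non-interval or ratio scale level or for non-normally distributed variables". The listed factors are group (two levels) and time (baseline, week 6, week 18). The section does not say which effect decides, and it makes no exception for the BAI.

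Study design places the first assessment before the intervention. Neither that section nor the inclusion criteria say whether the qualifying BAI is reused as the baseline value.

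**The concern.** A one-week symptom score fluctuates. Patients admitted because a reading exceeded a cut were, on average, a little above their usual level that week, so their next readings tend to be lower without treatment. If the qualifying reading is the first time level, a test of time picks up that fall.

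In a randomised trial this is normally harmless, because both arms regress alike and the comparison between them cancels it. That protection works only if the comparison between arms is what is tested. Friedman's test ranks repeated readings within each patient and has no group factor, although the section lists group as one. Two features push the BAI towards that test. A baseline cut off at 26 is skewed, and a sum of ordinal self-ratings could be classed as non-interval. Following the plan as written could therefore leave the BAI judged on the one effect that the entry rule inflates.

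At stake is the anxiety result, in a population defined by anxiety. A fall in both arms could be reported as benefit when neither treatment had an effect.

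**Working it through.** **Inputs from the article.** Entry at BAI above 26; three time points; 18 patients randomised per arm, of whom 16 are needed as completers (Calculation of sample size). That calculation concerns the GSES, so there is no BAI figure to reproduce.

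**Assumed, because the article does not give them.** BAI in the source population normal with SD 10 and mean 15 to 35; retest reliability ρ of 0.7 to 0.9; stable true scores; no treatment effect in either arm; qualifying score used as baseline.

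**Expected fall.** With a = (26.5 − mean)/SD,

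fall = (1 − ρ) × SD × φ(a) / (1 − Φ(a)).

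- Mean 15, ρ 0.7: a = 1.15; ratio 0.206/0.125 = 1.65; fall = 0.3 × 10 × 1.65 = 4.9 points.
- Mean 20, ρ 0.75: a = 0.65; ratio 0.323/0.258 = 1.25; fall = 0.25 × 10 × 1.25 = 3.1 points.
- Mean 35, ρ 0.9: a = −0.85; ratio 0.278/0.802 = 0.35; fall = 0.1 × 10 × 0.35 = 0.35 points.

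**False-positive rates.** Simulation with 16 completers per arm and 3000 trials per row. Nominal level 5%.

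| Source mean | ρ | Simulated fall | Time, ANOVA | Time, Friedman (arms pooled) | Group × time | Friedman, separate baseline |
|---|---|---|---|---|---|---|
| 15 | 0.75 | 4.1 | 95% | 85% | 5.5% | 5.2% |
| 15 | 0.9 | 1.7 | 57% | 43% | 5.3% | 4.4% |
| 20 | 0.75 | 3.2 | 74% | 62% | 5.5% | 4.2% |
| 20 | 0.9 | 1.3 | 36% | 26% | 3.9% | 4.2% |
| 25 | 0.75 | 2.3 | 45% | 35% | 5.4% | 4.7% |
| 25 | 0.9 | 0.9 | 19% | 14% | 4.9% | 4.3% |
| 30 | 0.75 | 1.4 | 21% | 17% | 5.3% | 5.0% |
| 30 | 0.9 | 0.6 | 11% | 9% | 5.2% | 4.0% |
| 35 | 0.75 | 0.8 | 10% | 8% | 5.0% | 5.1% |
| 35 | 0.9 | 0.3 | 7% | 6% | 4.7% | 5.0% |

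A second simulation, with all 36 patients and scores rounded and kept within 0 to 63 (assumed scale), gives 95% for Friedman's test at mean 15, ρ 0.7; 82% at mean 15, ρ 0.8; 54% at mean 20, ρ 0.8; and 16% at mean 25, ρ 0.9. A t-test of the week-6 change between arms stays at 4% to 6% in every scenario of the first simulation, even with the qualifying score as baseline.

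**Route to Friedman's test.** The article does not name a normality check. If Shapiro-Wilk were applied to a reused baseline BAI in 36 patients, it would reject in 86% to 99% of trials at source means 15 to 25 and in about 70% at mean 30, with fewer rejections above that. A separate baseline reading is not truncated at the cut, so these rejection rates do not apply to it.

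**The case against.** The strongest reply is that the trial is randomised and the same threshold applies to both arms. The stated hypothesis is comparative: "We hypothesize that the BEWARE intervention will be more effective than physical therapy alone (TAU) in improving self-efficacy". The group-by-time test keeps its level throughout the table, and on the ANOVA branch that test is available. This stands. A reader might infer that the BEWARE-versus-TAU comparison is biased, or that the main conclusion is at risk. The documents support neither: the GSES is not an entry criterion and anxiety is a secondary outcome.

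Second, everything depends on the qualifying score being the baseline score, which the article does not state. This stands as a condition. With a separate baseline the expected fall is about zero and the error rate about 5%.

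Third, clinicians are asked to approach patients whom they already judge to have wearing-off related anxiety, so the source mean may be high and the inflation small. This is fair. It is why the range extends to a mean of 35, where the effect nearly disappears.

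Fourth, nothing says that a fall over time will be read as efficacy. A reader might infer such an intention from the Discussion's remark "In the pilot study, we observed a decrease in BAI total score in the participating patients". That remark is motivation from four pilot patients, not an analysis rule.

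Fifth, the missing group factor affects every outcome sent to Friedman's test, and an article may leave analysis detail to the full protocol. The first part is true. But this article does fix a rule, and for the BAI that rule can select the one test that shows the selection effect and omits the comparison that would cancel it.

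**Conclusion.** The point holds in a conditional form. If the qualifying BAI is also the baseline BAI, a significant time effect on the BAI can arise with no treatment effect. The size depends on quantities that the article does not give. Over the assumed range, Friedman's test is significant in about 6% to 8% of such trials at a source mean of 35 (reliability 0.75 to 0.9), rising to about 95% at a mean of 15 and reliability 0.7. With a separate baseline reading it is about 5%. The time effect on the ANOVA branch is inflated in the same way, but there the between-arm test is at hand.

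It would be tempting to say that a significant fall is bound to appear. The figures do not support that, because several plausible scenarios lie close to the nominal level. Nor does the argument extend to the WOQ-19, the other entry instrument: its criterion is at least one symptom that improves after a dose, which is not a high cut, and no calculation shows material regression there.

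The consequence is limited to how the anxiety result is tested and read. It deserves correction because the change is nearly free.

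**What to change.** In Data analysis, add that the BAI is tested as the between-arm difference at weeks 6 and 18, adjusted for baseline BAI, in place of Friedman's test. A skewed baseline is no obstacle, since the model's normality assumption concerns the residuals, not the covariate. Add that time effects and within-arm falls in the BAI are not evidence of efficacy.

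State which BAI reading is the baseline. Where a separate BAI is completed at the baseline assessment, use that reading and not the qualifying score. If only the qualifying score exists, the adjusted between-arm comparison is still valid.

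The cost is two or three sentences and no new data collection. The downside is that within-arm improvements in anxiety can no longer be claimed as treatment effects.
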